Title:

A proactive approach to prevent non-communicable diseases through screening and educating emergency department attendees to adopt healthy lifestyles: A randomised clinical trial

Introduction:

Hong Kong is facing a growing burden of non-communicable diseases (NCDs), such as cardiovascular diseases, cancer, diabetes, and chronic respiratory diseases, exacerbated by an aging population. The World Health Organization has identified four major behavioural risk factors that substantially contribute to NCDs and can increase the risk of death: tobacco use, excessive alcohol consumption, an unhealthy diet, and physical inactivity. Most premature deaths from NCDs could have been prevented through lifestyle modifications.

In 2021, we conducted a large population survey (N = 5,737) in all 18 districts of Hong Kong to investigate the health-risk behaviours of Chinese adults. The results showed that 80.3% of the participants had at least one health-risk behaviour, and 47.0% of the participants had two or more health-risk behaviours. In response to the challenges posed by the increasing prevalence of NCDs, the government has committed to enhancing district-based primary healthcare services by establishing health centres in all districts across Hong Kong and launching the Chronic Disease Co-Care Pilot Scheme in 2023. However, many Chinese adults lack motivation or experience difficulty in adopting a healthy lifestyle, especially if they do not receive advice or support from healthcare professionals. In addition, the survey findings revealed that more than half of the participants had not undergone regular body check-ups or monitored their physical health at home in the past 3 years. Although regular body check-ups are crucial for preventing NCDs, a common misconception among many Chinese adults is that they do not need physical check-ups if they feel well. Thus **a proactive approach is required** to screen people with health-risk behaviours and help them adopt healthy lifestyles, including quitting smoking, avoiding excessive alcohol consumption, maintaining a balanced diet, and engaging in regular physical activity.

The receipt of medical attention at an ED by a person in physical discomfort can serve as an excellent 'teachable moment' because it provides an invaluable opportunity to initiate a healthy lifestyle. People who consult a doctor in an ED are more likely to modify their risk behaviours to improve their health. According to the Hospital Authority Annual Report, there were 1.8 million ED visits in Hong Kong between 2021 and 2022. More than half of all ED visits were triaged as semi-urgent (level 4) or non-urgent (level 5), and most of the patients were discharged home after receiving medical attention. A previous study found that 86.6% of patients admitted to and discharged from the ED on the same day had a high risk of NCDs, such as blood pressure exceeding 160/100 mmHg before discharge. Furthermore, more than 75% of these patients did not receive any referral or follow-up care. The proposed project will address the gaps in the literature and will align with the Health Bureau's thematic priority B-0002: 'Develop and test novel approaches for enhancing prevention, early diagnosis, treatment, and recovery/ rehabilitation from major NCD'.

Aim and Hypotheses to be Tested:

Aim

To examine the effectiveness of a general health promotion intervention based on self-determination theory in helping ED attendees adopt a healthy lifestyle.

Hypothesis to be tested

We hypothesise that a higher proportion of individuals in the intervention group will adopt healthy lifestyles and have a better health-related quality of life than those in the control group at 6- and 12-month follow-ups.

## Plan of Investigation:

### Study design

An assessor-blinded, multicentre RCT with a two-group between-subjects design will be used following the Consolidated Standards of Reporting Trial.

### Randomisation and allocation concealment

To prevent the potential risk of treatment contamination within the ED, randomisation will not be performed there. Instead, the research assistant (RA) will input baseline data collected at the ED directly into the web-based trial entry form linked to a computerised database. Subsequently, randomisation will be performed at the principal investigator's institution by an independent statistician who will have no other involvement in the study. Stratified block randomisation with 1:1 allocation will be conducted using varying block sizes of 4–10 to achieve an appropriate balance of participant numbers between the intervention and control groups and to optimise allocation concealment.

## Methods

### **Setting:**

The proposed project will be conducted at the EDs of five major acute care hospitals in different clusters in Hong Kong. The source of funding for this project is Health and Medical Research Fund (HMRF), Health Bureau.

### **Conceptual and theoretical framework:**

The proposed intervention is guided by the theory of planned behaviour, the foot-in-the-door technique, and self-determination theory.

#### *Theory of planned behaviour*

This theory holds that an intention to engage in a health-related behaviour is determined by the proximal factors of attitudes, subjective norms, and perceived behavioural control. Attitudes represent individuals' perceived likelihood of performing and appraisal of the consequences of performing a health-promoting behaviour. Subjective norms are the social pressure perceptions to either perform or not perform a health-promoting behaviour. Finally, perceived behavioural control is an individual's perception of control regarding performing the behaviour.

#### *Foot-in-the-door technique*

The foot-in-the-door technique, which was introduced by Freeman and Fraser, emphasises the notion that individuals who initially comply with a small, easy request are more likely to later comply with a larger request. Compliance with the first request or target increases the individual's confidence and alters their self-perceived capability and willingness regarding further requests or targets. This technique can facilitate the recruitment process and enhance compliance.

#### *Self-determination theory*

According to self-determination theory, behavioural regulation is more autonomous when it is internalised, as opposed to being regulated by external factors. Compared with external regulation, autonomous regulation is associated with increased self-efficacy, greater behavioural persistence, longer-term

behavioural changes and more positive health behaviour. Autonomy is another influential determinant of behaviour that is emphasised by freedom of choice. There is some evidence that people who have greater autonomy demonstrating greater competence and self-efficacy in achieving behavioural change compared with those with less autonomy. As a result, increased autonomy will facilitate a gradual change in risky behaviours.

Our intervention aims to first change the participants' attitudes and their subjective norms through risk communication. Using foot-in-the-door technique and self-determination theory, it will then increase participants' willingness to adopt a healthy lifestyle.

## **Recruitment**

### **At the EDs**

We will obtain ethical approval from the institutional review boards of the five hospitals. **All** potential participants will be approached by emergency nurses before being discharged from the EDs. These nurses will provide potential participants with a leaflet detailing the nature, purpose, design, procedures, and potential benefits and risks of the study. Subsequently, the emergency nurses will refer the potential participants to the RA. Informed written consent will be obtained from all participants. Participants will be assured that their participation will be voluntary, with no prejudice attached to refusal, and that the information provided by them will be kept confidential. A baseline assessment will be performed using questionnaires. Then, participants will be informed that they will receive a telephone call from an RA within 3 days to evaluate their potential health-risk behaviours and provide them with appropriate health advice to adopt healthy lifestyles. In addition, the participants will be provided a Practical Resource Hub for Healthy Life leaflet (Appendix 2) containing information on various applications, including (i) 'Move Your Body', (ii) 'Eat Healthy', (iii) 'Live Alcohol Free', and (iv) 'Stay Away from Tobacco', which were developed by the Hong Kong Department of Health.

## **Intervention**

### ***(a) Intervention group***

#### **Brief intervention via telephone (within 3 days after visiting the ED)**

The participants will receive a brief intervention using the Ask, Warn, Advise, Refer and Do-it-again (AWARD) model, which was originally developed for primary-care tobacco cessation. This intervention includes the following steps: (1) **Ask** about and assess health-risk behaviours; (2) **Warn** about the high morbidity and mortality risks associated with health-risk behaviours; (3) **Advise** on adopting healthy lifestyles to improve the participant's health; (4) **Refer** to hotline services, such as those for smoking cessation and alcohol treatment or the nearest district health centre to follow up their health status; and (5) **Do it again** if participants have not adopted a healthy lifestyle at follow-ups. For the advice step, the RA will ask about the participants' priority in engaging in a desired health-related lifestyle based on their responses in the behavioural risk factor questionnaire. The participants will also be asked to choose a goal that they consider most attainable, such as quitting or reducing smoking, consuming more vegetables or less fatty foods or sugary drinks, performing more exercise, or reducing alcohol consumption. Although the participants will be encouraged to adopt aspects of a healthy lifestyle sequentially, they will have the option to adopt them simultaneously if they feel confident in doing so. Each participant will receive a brief (approximately 5 minutes) individual intervention providing health advice on their selected lifestyle goal. The entire intervention will last approximately 10 minutes and may be extended if necessary.

At the end of the telephone call, the participant will be informed that the RA will assist them in achieving their health-related goals throughout the study by sending messages via WhatsApp/WeChat.

#### **Follow-up booster intervention (up to 6 months)**

During the first 6 months of the proposed project, the RA will send WhatsApp/WeChat messages approximately once a week to remind the participants to adhere to their desired health-related lifestyle. Instant messaging via mobile applications was found to be effective in enhancing treatment compliance.

In addition, during the first week, the RA will send participants a link via WhatsApp/WeChat to a 1-minute video developed by the research team comprising content relevant to their selected health-related lifestyle. Four separate 1-minute videos will be compiled, each focusing on a different healthy lifestyle. These videos will indicate the health hazards of continuing this health risk behaviour and the benefits of adopting a healthy lifestyle. Moreover, the RA will encourage the participants to watch the video and ask any questions regarding the video content via WhatsApp/WeChat. One advantage of using videos to deliver instant health advice messages is the use of sound and images, which can elicit emotions, enhance understanding of abstract concepts, and improve the retention of new information through auditory, visual, and verbal stimulation. Moreover, the delivered content can be viewed by the participants at their convenience and own pace.

#### Follow-up assessment of behavioural changes at 3, 6, and 12 months

The success of the participants in achieving their targeted health-related lifestyle will be assessed through phone calls at 3, 6, and 12 months. If the participants report the successful adoption of a healthy lifestyle, the RA will encourage them to adopt another healthy lifestyle. Then, the RA will provide participants with brief healthcare advice (approximately 5 minutes) and send via WhatsApp/WeChat another 1-minute video focused on their newly chosen and desired health-related lifestyle.

#### *(b) Control group*

Participants will receive a brief telephone intervention based on the AWARD model from the trained RA, similar to that delivered to the intervention group. However, the RA will only advise the participants to adopt a healthy lifestyle. In addition, the RA will send regular SMS messages to participants at a frequency similar to that used for the intervention group. However, these messages will contain only general health advice. In addition, the participants will receive follow-up outcome assessments at the same schedule as that followed in the intervention group.

#### Training and quality assurance

Prior to the study initiation, the PI and Co-Investigators (Co-Is) will conduct a training workshop for the RAs. The training will equip the RAs with the necessary knowledge and skills required to deliver a brief intervention based on the AWARD model and provide healthcare advice on various health-related lifestyles. Regular case conferences and quality assessments will be conducted through audiotaping, and audits will be conducted to ensure the quality and uniformity of the interventions.

#### Subjects

Chinese adults who attend one of the five EDs in various clusters in Hong Kong because of physical discomfort and if they meet the following criteria will be invited to participate. The inclusion criteria will be as follows: (1) being aged  $\geq 18$  years, (2) being triaged as semi-urgent (level 4) or non-urgent (level 5) and discharged home on the same day after receiving medical attention, (3) having at least one health risk behaviour (tobacco use, harmful alcohol consumption, unhealthy diet, and physical inactivity), and (4) owning a smartphone and having an ability to use instant messaging applications (e.g. WhatsApp or WeChat). The Exclusion criteria will be as follows: (1) having a poor cognitive state or mental illness and (2) being diagnosed with NCDs and undergoing regular follow-ups in outpatient clinics, and (3) participating in another related study.

The specific criteria for each health risk behaviour are listed in Appendix 1. People who do not have a smartphone or use WhatsApp/WeChat (unlikely in Hong Kong) will be provided brief advice and a Practical Resource Hub for Healthy Life leaflet on healthy lifestyles but will be excluded from the study.

### **Sample size**

We used G\*Power to estimate the sample size based on the results of our pilot study conducted at an ED and a previous study using a brief smoking cessation intervention based on self-determination theory. The results of the pilot study showed an approximately 12% between-group difference in successfully adopting at least one healthy lifestyle at 6 months (the primary outcome of this proposed project). However, we opted for a more conservative effect size for our sample size calculation. Based on our previous large-scale RCT on a brief smoking cessation intervention based on self-determination theory, we expect a between-group difference of at least 5% ( $\geq 10\%$  in the intervention group vs.  $\leq 5\%$  in the control group) in the primary outcome at 6 months. To detect a significant between-group difference with a power of 80% at a significance level of 5% (two-tailed) in the proportion of participants modifying their health risk behaviours and/or adopting healthy lifestyles, 435 participants will be needed per group. To account for a potential attrition rate of 30% at the 6-month follow-up, we will recruit a total of 1,242 participants.

Based on the number of EDs visits (1.8 million) in Hong Kong between 2021 and 2022, we are confident that we will be able to recruit the required number of participants within 18 months.

### **Data processing and analysis**

#### **Instruments:**

We will use available objective assessment tools to supplement the participants' self-reported outcomes to determine changes in their health-risk behaviours after the intervention. For verifying smoking cessation, we will use the biochemically validated 7-day point prevalence of abstinence, determined by a saliva cotinine level of  $<115$  ng/ml and an exhaled carbon monoxide level below  $<4$  ppm. Only those who meet both these criteria will be regarded as biochemically validated abstinent individuals; otherwise, the participants will be considered to have failed the validation. HK\$200 supermarket coupon being the incentive for completing biochemical validations

**A behavioural risk-factor questionnaire** will be used as the patient-report outcome measure to collect data on eligible participants' demographic and health-risk behaviours (tobacco use, binge drinking, unhealthy diet and physical inactivity) at baseline and at 3, 6, and 12 months. Moreover, participants' blood pressure and body mass index will be documented. This questionnaire was used to investigate multiple health-risk behaviours among Chinese adults in Hong Kong in 2021.

**The EuroQoL 5-Dimension 5-level (EQ-5D-5L)** will be used to assess the participants' health-related quality of life at baseline, 6 months, and 12 months. The psychometric properties of the Chinese version of the EQ-5D-5L were tested, and the findings indicate that this tool is a valid, reliable, and sensitive measure of health-related quality of life. A Chinese-specific EQ-5D-5L value set will enable the calculation of health utility scores applicable to the Chinese population and quality-adjusted life-years (QALYs) for conducting cost-effectiveness analysis.

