**Appendix 1**

Criterion for determination of each health-risk behaviour and criteria of successful adopting a healthy lifestyle

| Behavioural risk factors  | Criterion of health-risk behaviour                                                                                                                                                                          | Successful criteria of adopting a healthy lifestyle                                                                                                                                               |
|----------------------------------|--------------------------------------------------------------------------------------------------------------------------------------------------------------------------------------------------------------------|----------------------------------------------------------------------------------------------------------------------------------------------------------------------------------------------------------|
| Tobacco use          | Smoked at least 1 cigarette a day over the past 30 days                                                                                                                                                            | Self-reported 7-day point prevalence of smoking abstinence                                                                                                                                               |
| Binge drinking       | Reporting $\geq 1$ binge drinking episodes (consumption of five or more alcoholic beverages on one occasion) in the past month.                                                                                    | Self-report no binge drinking episode (consumption of five or more alcoholic beverages on one occasion) in the past month.                                                                               |
| Unhealthy diet       | Have consumed less than five servings of fruit and vegetables per day or have had a daily intake of less than 400 grams of fruit and vegetables                                                                    | Have consumed at least five servings of fruit and vegetables per day or have had a daily intake of at least 400 grams of fruit and vegetables                                                            |

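### Saliva cotinine below 115 ng/ml with CO below 4 ppm is labelled validated 7-day abstinence, but on a wide range of assumed kinetics it can verify only recent abstinence and can pass a light smoker

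*Protocol*

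**What the plan says.** Under Data processing and analysis, Instruments, the protocol introduces objective measures with "We will use available objective assessment tools to supplement the participants' self-reported outcomes". For smoking it states "we will use the biochemically validated 7-day point prevalence of abstinence", fixed as "determined by a saliva cotinine level of $<115$ ng/ml and an exhaled carbon monoxide level below $<4$ ppm". The two tests are joined by a strict rule: "Only those who meet both these criteria will be regarded as biochemically validated abstinent individuals". Anyone else who is tested fails validation. No citation, rationale, sensitivity or specificity is given for the cotinine threshold.

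Appendix 1 defines the tobacco user by "Smoked at least 1 cigarette a day over the past 30 days" and tobacco success by "Self-reported 7-day point prevalence of smoking abstinence". The Outcome measures section takes its success criteria from Appendix 1. Validated abstinence is named neither as a primary nor as a secondary outcome.

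**The concern.** The label makes two demands on the test. It should separate someone who has stopped from someone the trial still counts as a tobacco user, and that category starts at one cigarette a day. It should also say something about the whole of the previous seven days.

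On the assumed half-lives, exhaled CO reflects hours, so any look-back of several days has to come from cotinine. A cotinine threshold can give that look-back only if it is low compared with what light smoking produces and with what remains after a day or two without cigarettes. A threshold of 115 ng/ml looks high on both counts.

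At stake is the meaning of the validated quit rate. This is the only objective check on a behaviour that the protocol specifies. If it passes people who still smoke a little, or who paused for a day or two, it gives more reassurance about the self-reports than it has earned.

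**Working it through.** **Inputs from the protocol.** Cotinine below 115 ng/ml and CO below 4 ppm, both required; 7-day window (168 h); tobacco user from 1 cigarette a day; tobacco success in the primary outcome by self-report.

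**Inputs assumed, because the protocol gives none.** Steady-state saliva cotinine of 5 to 30 ng/ml per daily cigarette; starting cotinine of 200 to 500 ng/ml; cotinine half-life 12 to 24 h; starting CO of 10 to 30 ppm; CO half-life 2 to 8 h; first-order decay.

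**1. The plan's own reproducible figure.** The protocol derives no cut-off, so the only figure to reproduce is the sample size. For 10% versus 5%, two-sided 5%, 80% power, pooled variance:

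n = [1.96·√(2·0.075·0.925) + 0.8416·√(0.10·0.90 + 0.05·0.95)]² / 0.05² = (0.7301 + 0.3121)² / 0.0025 ≈ 434.4, so 435 per group, as stated.

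With 30% attrition, 870/0.7 = 1,242.9, against the stated 1,242. The cotinine threshold does not enter.

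**2. Smoking level that corresponds to the threshold.** Cigarettes a day = 115 / (ng/ml per daily cigarette).

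- At 5 ng/ml: 115/5 = 23.
- At 30 ng/ml: 115/30 = 3.8.

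A 1-a-day smoker would sit at 5 to 30 ng/ml and pass the cotinine test. To fail it, that smoker would need 115 ng/ml from a single daily cigarette.

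**3. Time without smoking needed to pass.** Hours = half-life × log2(start / cut-off). The 15 ng/ml column is for comparison.

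| Start (ng/ml) | Hours to 115 (half-life 12–24 h) | Hours to 15 (half-life 12–24 h) | Level after 168 h (ng/ml) |
|---|---|---|---|
| 200 | 9.6–19.2 | 44.8–89.7 | 0.01–1.56 |
| 300 | 16.6–33.2 | 51.9–103.7 | 0.02–2.34 |
| 500 | 25.4–50.9 | 60.7–121.4 | 0.03–3.91 |

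For a mid-range case (start 250 ng/ml, half-life 16 to 20 h), log2(250/115) gives 18 to 22 h and log2(250/15) gives 65 to 81 h.

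After a true seven days every starting level in the table is below 4 ng/ml. To be still at 115 ng/ml after seven days with a 24 h half-life, the start would have to be 115 × 2⁷ = 14,720 ng/ml.

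**4. Whether the CO test closes the gap.** Hours to 4 ppm = half-life × log2(start / 4).

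- From 10 ppm at 2 h: 2 × log2(2.5) = 2.6 h.
- From 30 ppm at 8 h: 8 × log2(7.5) = 23.3 h.

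CO can fail a daily smoker tested soon after a cigarette. It does not block someone who has not smoked for up to about a day.

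**5. Where the result is used.** Appendix 1 counts self-reported abstinence, and Data Analysis models the self-reported number of lifestyles. Changing 115 to any other value leaves both as they are.

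**The case against.** The strongest reply is that no named outcome depends on this number. That stands. Tobacco success is self-reported, and the tests are there to supplement it.

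Second, the protocol does not contradict itself. Its definition of a tobacco user carries no cotinine level, and the conflict appears only once outside kinetics are assumed. This also stands, so the point is conditional and needs its ranges. The qualitative result nevertheless holds over every range tried.

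Third, passing takes more than light smoking. The participant must also report seven days' abstinence falsely and have cleared CO. At 30 ng/ml per daily cigarette, a 5-a-day smoker would be at 150 ng/ml and would fail. So a reader should not infer that light smokers always pass, or that one day off cigarettes is always enough; a heavy smoker may need about two.

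Fourth, a lower threshold is no clean cure. At 5 to 8 ng/ml per daily cigarette, a 1-a-day smoker still passes at 10 to 15 ng/ml. Seven days remain unverified. A quitter on nicotine replacement could fail on cotinine, and a low CO could not rescue that person under the both-tests rule. This is why the lower cut-off should be reported beside 115 rather than substituted for it.

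**Conclusion.** The point holds in a limited form. The threshold is given without rationale and does not do what its label says. On the assumed kinetics it corresponds to about 4 to 23 cigarettes a day and is passed after about 10 to 51 h without smoking, against a claimed window of 168 h. A light or recently paused smoker who claims abstinence can pass both tests.

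The effect is confined to the supplementary validated quit rate and what is concluded from it. Three stronger readings are tempting, and the protocol supports none of them:

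- **That the primary result is inflated or the sample size wrong.** Neither uses the threshold. This would change only if the sponsor meant a failed validation to override self-report, which the current text does not say.
- **That the bias favours the intervention arm.** The control arm also receives a call based on the same advice model, and nothing in the protocol gives a difference in false reporting between arms.
- **That the test confirms most false claims.** That would need the number of false reporters, their consumption and the timing of the tests. None of these is given.

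**What to change.** - Have the assay report cotinine as a concentration, on the saliva sample already planned.
- State the rationale for 115 ng/ml. Prespecify validated abstinence also at a lower cut-off chosen against the 1-cigarette-a-day definition, and report both results. On the assumptions above the order is 10 to 15 ng/ml: 15 ng/ml corresponds to 15/30 = 0.5 up to 15/5 = 3 cigarettes a day.
- Record nicotine-replacement use at the time of the test, so that those participants can be identified in the stricter result.
- Describe the test as verifying recent abstinence, about 1 to 3 days at mid-range kinetics (18 to 22 h at 115 ng/ml, 65 to 81 h at 15 ng/ml), and not seven days. Even the slowest case in the table, 121 h at 15 ng/ml, falls short of 168 h.

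The cost is small: a change of wording, an assay instruction, one extra question and one extra line of results. The drawbacks are a lower validated quit rate at the stricter cut-off and possible misclassification of nicotine-replacement users. Keeping the 115 ng/ml result preserves comparability with work that used it.

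### The two-marker rule for validated smoking abstinence makes no provision for non-smoked nicotine, so some true quitters can be recorded as failed validations (a minor point that does not touch the primary outcome)

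*Protocol*

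**What the plan says.** The Protocol, under Instruments, introduces the biochemical tests as an addition to self-report: "We will use available objective assessment tools to supplement the participants' self-reported outcomes". Abstinence over the past 7 days is validated by two markers. One is "determined by a saliva cotinine level of" less than 115 ng/ml; the other is "an exhaled carbon monoxide level below" 4 ppm. The rule is closed at both ends: "Only those who meet both these criteria will be regarded as biochemically validated abstinent individuals", and "otherwise, the participants will be considered to have failed the validation". No exception, third category or question about nicotine products is given, and no validation visit or schedule is named. The follow-up assessments themselves are telephone calls.

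In the intervention arm, the Refer step of the AWARD call directs participants "to hotline services, such as those for smoking cessation and alcohol treatment", or to a district health centre. The control arm section first describes a comparable AWARD-based call and then limits it: "However, the RA will only advise the participants to adopt a healthy lifestyle".

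The Outcome measures section takes the success criteria for the primary outcome from Appendix 1. There the criterion for tobacco is "Self-reported 7-day point prevalence of smoking abstinence", with no biochemical requirement. Validated abstinence is not listed as a primary or secondary outcome.

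**The concern.** The behaviour being verified is smoking. Appendix 1 defines the risk by cigarettes smoked and success by not smoking. Exhaled carbon monoxide reflects inhaled smoke. Cotinine is a metabolite of nicotine and does not show whether the nicotine came from a cigarette or from a replacement product. Someone who meets the Appendix 1 criterion honestly, and passes on carbon monoxide, can still be classed as a failed validation on cotinine.

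Two things are at stake. The validated quit rate would be too low. And since this is the only biochemical check on quitting that the Protocol describes, a shortfall of validated against self-reported quitters would be read as misreporting when part of it is nicotine use without smoking. If nicotine use is not recorded at the time of the test, the two explanations cannot reliably be separated afterwards.

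**Working it through.** **Does the point touch the planned sample size?** No. The Sample size section gives 435 per group for 10% against 5%, two-sided 5% level, 80% power. The pooled two-proportion formula reproduces it:

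n = [1.96 × √(2 × 0.075 × 0.925) + 0.8416 × √(0.10 × 0.90 + 0.05 × 0.95)]² / 0.05² = 434.4, rounded up to 435.

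Nothing in this depends on the validation rule.

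**Does it touch a listed outcome?** Outcome measures points to Appendix 1, where tobacco success is self-reported. The count at 12 months is the same measure at a later time, and the GEE model in Data Analysis is for self-reported lifestyles. The rule acts only on the supplementary validated rate.

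**How large could the loss be?** Let A be the true abstinence rate, u the share of true quitters using non-smoked nicotine when tested, and c the share of those users at or above 115 ng/ml. Assume every true quitter is tested and passes on carbon monoxide, and that nobody is validated wrongly. Then

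share of true quitters lost: L = u × c

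validated rate: V = A × (1 − L)

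The Protocol gives no value for u or c, and no quit rate among smokers. For A, I borrow the planning figures of 10% and 5%. They were set for the primary outcome in all participants, who can enter with any one of four risk behaviours, so using them for smokers is an assumption.

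| Lost, intervention | Lost, control | Validated, intervention | Validated, control | Difference (points) | Ratio |
|---|---|---|---|---|---|
| 0% | 0% | 10.0% | 5.0% | 5.0 | 2.00 |
| 10% | 10% | 10 × 0.90 = 9.0% | 5 × 0.90 = 4.5% | 4.5 | 2.00 |
| 15% | 5% | 10 × 0.85 = 8.5% | 5 × 0.95 = 4.75% | 3.75 | 1.79 |
| 30% | 10% | 10 × 0.70 = 7.0% | 5 × 0.90 = 4.5% | 2.5 | 1.56 |

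The third row is what remains of the fourth if only half of the users reach the cut-off (30% × 0.5 = 15%, 10% × 0.5 = 5%). With equal losses the difference shrinks but the ratio is unchanged; only unequal losses move the ratio. I give no power figure, because the number of smokers is unknown and the Protocol specifies no test of the validated rate.

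**The case against.** The best defence is that the rule is clear, strict and fixed in advance, that it contradicts nothing else in the Protocol, and that it governs a supplementary measure. A question on nicotine use and a sensitivity analysis are often left to a case report form or an analysis plan. The limited impact stands in full. The last argument stands only in part: the Protocol does not leave the classification open. It states a rule that sends everyone who misses either criterion to failure, and that stated rule misclassifies some quitters.

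A reader might go further and infer that the check penalises the intervention arm because that arm is referred to cessation services, and could even reverse the result on smoking. The arithmetic allows it: with losses of 30% and 10%, any true ratio below 0.9 / 0.7 = 1.29 would reverse. The documents do not support the premise. The control call is also based on AWARD, which contains a Refer step, and the sentence limiting controls to advice does not settle whether that step is dropped. The Protocol never mentions nicotine replacement. Not every user would reach 115 ng/ml, and the documents give no share.

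There is also a fair objection to relaxing the rule. Judging declared nicotine users on carbon monoxide alone makes validation depend partly on self-report again, with a marker that has a shorter detection window. If one arm has more users, the looser test is applied more often there.

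**Conclusion.** The point holds as a minor one. The rule as written can record a true quitter as a failed validation when non-smoked nicotine brings cotinine to the cut-off. This would lower the validated quit rate and make some honest reports look false.

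The size cannot be derived from the Protocol. In the illustrations, a true 5.0-point difference appears as 4.5, 3.75 or 2.5 points. These rest on three assumptions: that some quitters use nicotine products when tested, that a given share of them reach 115 ng/ml, and that the planning rates carry over to smokers. A difference between arms is possible but not established.

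It should not be read as a threat to the trial's main result. The primary outcome and the 12-month count use self-reported abstinence under Appendix 1 and would not change.

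**What to change.** At each biochemical validation, record whether the participant has used nicotine replacement or any other non-smoked nicotine in the past 7 days. State under Instruments that validated abstinence will be reported by arm in two ways: under the strict two-marker rule, and with declared nicotine users judged on the carbon monoxide criterion alone while both criteria are kept for everyone else. Give the number reclassified in each arm. It would also help interpretation to reconcile the two sentences on the control call, so that it is clear whether controls are referred.

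The cost is one question, a sentence or two of text and one extra result. Because no validation visit is scheduled in the Protocol, the question belongs to whatever occasion is used for the tests. The drawback is that the exception relies on declared use and on a marker with a shorter window, so it may pass a few recent smokers and could favour the arm with more users. Showing both results side by side makes that visible.
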